## Abstract

**Background:**

The medical community is beginning to recognize that retinitis pigmentosa (RP), due to its disabling progression, eventually leads to a reduction in the patient´s quality of life, a direct economic impact, and an increase in the burden on the health care system. There is no curative treatment for the origin of the disease, and most of the current interventions fail in reducing the associated negative psychological states, such as anxiety and depression, which lead to increased variability of vision and pose a continuous threat to the patient’s independence.

**Objective:**

The aim of this study is to assess the effect of oral melatonin (OM) administration alone and combined with short-wavelength light (SWL)–blocking filters on patients with RP and test their effectiveness in improving the level of stress and sleep problems in many of these patients.

**Methods:**

We have developed a low-cost therapy protocol for patients with RP with sleep disorders and negative psychological stress. Patients will be randomized to receive a combined intervention with SWL-blocking filters and OM, SWL-blocking filters alone, or OM alone. There will also be a nonintervention arm as a control group. This study will be conducted across 2 retinal units in patients with RP with sleep disorders and high perceived stress and anxiety score reports. Patients will be assessed in the preintervention period, weekly during the 4 weeks of intervention, and then at 6 months postintervention. The primary outcomes are the differences in changes from baseline to postintervention in hormone release (α-amylase, cortisol, and melatonin) and sleep quality, as measured with the visual analog scale. Secondary outcome measures include clinical macular changes, as measured with optical coherence tomography and optical coherence tomography angiography; retinal function, as measured using the visual field and best-corrected visual acuity; sleep data collected from personal wearables; and several patient-reported variables, such as self-recorded sleep diaries, quality of life, perceived stress, and functional status.

**Results:**

This project is still a study protocol and has not yet started. Bibliographic research for information for its justification began in 2020, and this working group is currently seeking start-up funding. As soon as we have the necessary means, we will proceed with the registration and organization prior to the preliminary phase.

**Conclusions:**

In this feasibility randomized clinical controlled trial, we will compare the effects of SWL blocking alone, administration of OM alone, and a combined intervention with both in patients with RP. We present this study so that it may be replicated and incorporated into future studies at other institutions, as well as applied to additional inherited retinal dystrophies. The goal of presenting this protocol is to aid recent efforts in reducing the impact of sleeping disorders and other psychological disorders on the quality of life in patients with RP and recovering their self-autonomy. In addition, the results of this study will represent a significant step toward developing a novel low-cost therapy for patients with RP and validating a novel therapeutic target.

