The aim of this study is to assess the efficacy of OM combined with SWL-blocking filters in patients with RP who have sleep disorders and stress compared to any intervention alone or no intervention. We hypothesized that both interventions would improve their sleep quality, reduce their perceived stress levels, and shift their circadian rhythm to morningness.

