A draft intervention protocol will be developed for each group, covering preintervention, intervention, postintervention, and discharge settings based on the literature. A steering committee comprising ophthalmologists, opticians, nurses, psychologists, and the research team will be created to develop these protocols. Additionally, 2 ophthalmology residents will be included. Finally, 1 patient with RP, who is the current president of the Federation of Inherited Retinal Dystrophies’ Associations, will be included in the steering committee. The steering committee members are experts in their respective fields and have used the existing literature (summarized in the *Background and Rationale* section) to inform the inclusion of the different interventions in the protocols. The draft intervention protocols are presented in Table 1. Although the choice of each intervention in these protocols will be informed by the literature [7,28,30,36,51,57,67,75-82] and expert consensus of the steering committee, the study will assess the efficacy of combined interventions in sleep disorders and stress control in a large group of patients with RP. Before the intervention period, all patients will be asked to complete sleep diaries for 2 weeks. In addition, patients in the intervention groups (SWL, OM, SWL+OM) must complete them during the intervention period (30 days). Patients from the SWL and SWL+OM groups will wear SWL-restricting goggles in bright-light conditions and when using light-emitting diode (LED) electronic devices for the 30 days of intervention. Patients from the OM and SWL+OM groups will take 3 pills of Circadin 2 mg (OM) every evening at 10:00 P.M. with a margin of 30 minutes before and after.

A preintervention time of 1.5 years will be necessary for recruitment, informed consent, eligibility screening, and baseline data collection. Next, patients will be randomized to 4 groups in a 1:1 ratio. The treatment groups will include SWL with or without the use of OM. The control group will include patients who are eligible for the study but not willing to be randomized to an intervention sleep and stress management pathway. When the intervention phase (4 weeks) is over, all patients will be followed up for 6 months via standard monitoring. Figure 2 provides a summary of the RCT timeline.

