#### Adherence

Adherence monitoring will be performed to find new strategies to avoid attrition during the study and to look for unexpected problems that may prevent patients from attending the sessions. Patients will receive weekly phone calls to confirm appointments and obtain educational instructions about the study protocols to reassure them of the importance of adherence. Upon discharge, patients will be provided with instructions to contact their physician for unacceptable levels of sleep disability or perceived stress to receive an outpatient prescription of antianxiety medications and lifestyle techniques. Additionally, if a patient deviates from the intervention protocol assigned to them, they will not be considered a study failure. Instead, we will continue to follow the patient through study completion and continue to track patient-reported outcomes.

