#### Primary Outcome Measures

The primary outcomes are the differences in changes from baseline to postintervention in hormone release (sAA, cortisol, and melatonin levels in salivary and hair samples) and sleep quality, as measured by the ESS and the PSQI.

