#### Secondary Outcome Measures

Secondary outcome measures include any clinical macular changes or retinal function measured with the ETDRS scale, CSV-1000 chart, and ancillary tests, such as the VFI, OCT, and OCTA. In addition, several patient-reported variables, such as self-recorded sleep diaries, perceived stress, and functional status will be recorded.

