### Statistical Analysis

#### Sample Size Calculation

A sample size estimation of 48 patients (n=12, 25%, per group) was calculated for a target power of 80% and considering an α (probability of rejecting a true null hypothesis) of 5% and an actual power of 80.02%. Cohen d was 1.2 [101]. Due to the possible overestimation of the effect size in pilot studies, an effect size of 0.6 (medium-high) was chosen for this study. We calculated a total sample size of 60 participants (a total of 15, 25%, patients per group), adding approximately 20% (3 more patients per group than before) to manage possible dropouts [102-105].

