### Conclusion

Preservation of vision in retinal degeneration is one of the priorities of the World Health Organization Vision 2020 program. Clinical trials of melatonin in the context of controlling RP, for example, warrant serious consideration. Furthermore, positive results of such studies would not only benefit patients with various ocular disorders but also be particularly helpful in countries where the treatments are expensive and not easily accessible.

This protocol for a double-blind RCT aims to shed light on the benefits that OM combined with SWL-blocking filters might have for patients with moderate or severe RP in terms of disease progression and quality of life. The goal is that this protocol be replicated for future studies, applied to additional inherited retinal dystrophies, and potentially incorporated into clinical practice. Should this study demonstrate the superiority of the combined intervention versus no intervention, its findings may also help reduce the impact of sleeping disorders and negative psychological disorders on the quality of life of patients with RP and help them recover their self-autonomy.

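### The abstract calls this a feasibility trial, but no feasibility outcome is named and the plan leads to an efficacy judgment that 12 to 15 patients per arm would support poorly if the true effect is the chosen 0.6 SD

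*Protocol article*

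**What the plan says.** The label appears once, in the abstract's Conclusions: "In this feasibility randomized clinical controlled trial, we will compare the effects of SWL blocking alone, administration of OM alone".

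The remaining text describes an efficacy trial:
- Background and Rationale: "The aim of this study is to assess the efficacy of OM combined with SWL-blocking filters in patients with RP".
- Methods, Overview: "the study will assess the efficacy of combined interventions in sleep disorders and stress control in a large group of patients with RP".
- Primary Outcome Measures: "The primary outcomes are the differences in changes from baseline to postintervention in hormone release", together with the two sleep questionnaires.
- Secondary Outcome Measures: "Secondary outcome measures include any clinical macular changes or retinal function measured with the ETDRS scale", followed by further visual and imaging tests and patient-reported variables.
- Missing Data: the intention-to-treat and the completers' analyses must both favor the intervention before it counts as better than standard.
- Conclusion: "Should this study demonstrate the superiority of the combined intervention versus no intervention, its findings may also help reduce".

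Two places come near to feasibility. The legend of Figure 1 says that receipt, non-receipt with its reason, loss to follow-up and discontinuation will be registered. The Adherence section says "Adherence monitoring will be performed to find new strategies to avoid attrition during the study". Neither is made an outcome or given a target.

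On size, the Sample Size Calculation gives 12 per group for 80% power, cites a Cohen d of 1.2, and continues: "Due to the possible overestimation of the effect size in pilot studies, an effect size of 0.6 (medium-high) was chosen for this study". It then allows about 20% for dropout, which gives 15 per group and 60 in total.

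**The concern.** A feasibility trial and an efficacy trial are judged by different things. Under the first label, readers expect to learn whether patients can be recruited, kept and treated as planned. Under the second, they expect a contrast with adequate power. The article gives the first label and the outcomes of the second, so it is unclear what the trial is meant to conclude.

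The sample-size section itself warns that small studies tend to overestimate effects. If a favorable-or-not rule is then applied to 12 to 15 patients per arm, and the contrasts that pass it are taken at face value, the trial risks the error it warns about.

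**Working it through.** **Inputs.** All are from the Sample Size Calculation unless noted: 12 per group before dropout, 15 after; alpha 5% (sidedness not stated, two-sided assumed); d = 1.2 cited, 0.6 chosen; stated power 80.02%. Expected dropout is 5-10% (Missing Data). The test is taken as a single unadjusted two-sample t test with df = 2n − 2 and noncentrality d·√(n/2).

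**1. The plan's own figure.** For d = 1.2 and n = 12, the noncentrality is 1.2 × √6 = 2.94 and power is 80.2%, against 80.02% stated. Dropout: 12 / (1 − 0.20) = 15 per group, 60 in total. So 12 per group follows from 1.2.

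**2. Power at the chosen 0.6.**
- n = 12: noncentrality 0.6 × √6 = 1.47, power 29.0%.
- n = 15: noncentrality 0.6 × √7.5 = 1.64, power 35.5%.
- 80% power needs 45 per arm (80.4%), about 180 in total.

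**3. Smallest observed d that reaches p < 0.05.** This is t(0.975, 2n − 2) × √(2/n).
- n = 12: 2.074 × 0.408 = 0.85.
- n = 15: 2.048 × 0.365 = 0.75.

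Both exceed 0.6, so any observed d that is significant is larger in size than a true 0.6.

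**4. Average overstatement among significant results.** This is the mean absolute estimate among significant results divided by the true effect (400,000 simulated comparisons per setting). The lower figure in each cell uses the raw difference in true SD units, the higher one the observed standardized d.

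| True d | n per arm | Share significant | Ratio |
|---|---|---|---|
| 0.6 | 12 | 29% | 1.77 to 1.91 |
| 0.6 | 15 | 35.5% | 1.62 to 1.71 |
| 1.2 | 12 | 80% | 1.11 to 1.16 |
| 1.2 | 15 | 89% | 1.06 to 1.10 |

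Expected dropout of 5-10% leaves 15 × 0.95 = 14.25 to 15 × 0.90 = 13.5 per arm. The ratios at 14 and 13 per arm (1.66 to 1.83) lie inside the range for d = 0.6. A Bonferroni correction for three comparisons at d = 0.6 would raise the range to about 1.8 to 2.2. Over all simulated comparisons, significant or not, the mean raw difference equals the true 0.6.

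**5. What 60 patients can say about retention.** If 54 of 60 are retained (90%), the Wilson 95% interval is [0.9 + 0.032 ± 1.96 × √(0.0015 + 0.000267)] / 1.064 = 79.9% to 95.3%. This is a usable estimate, but it only just separates 10% dropout from 20%.

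**The case against.** The strongest reply is that this is a one-word slip. The label stands only in the abstract, while the aim, outcomes, power target and decision rule all describe an efficacy trial, so the word could simply go. It is true that the label appears once and that deletion is a legitimate choice. But deletion leaves a trial whose power was worked out for 1.2 while 0.6 is said to be chosen, and the overstatement in the working comes from that gap.

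A second reply is that feasibility information is already collected. In part it is, through the Figure 1 counts and the adherence monitoring. This makes the repair cheap, but the article lists its outcomes and none of these counts is among them. Detailed progression criteria may well be left to the full protocol, and their absence is not part of this point.

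A third reply is that the t test is a simplification. The planned hormone analysis is a linear mixed model with saliva taken at baseline and at four weekly visits, which may gain precision and lower the ratio. This stands. The article gives no correlation, so the gain cannot be computed.

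A reader might also infer more than the text supports:
- That the trial promises to validate a therapeutic target. The abstract speaks only of a step toward doing so.
- That it is bound to claim superiority. The Conclusion is conditional.
- That a later trial would be planned too small from these results. No such planning is described.

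**Conclusion.** The point holds in a conditional form. The feasibility label does not match the outcomes, the aim, the decision rule or the foreseen conclusion, and the passages need to be brought into agreement.

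The size is this: with a true effect of 0.6 SD, 12 to 15 patients per arm and one two-sided 5% t test, power is about 29% to 36%. Results selected for significance overstate the effect by about 1.6 to 1.9 times on average.

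A reader might take this to mean that the trial will report inflated effects whatever happens. The documents do not support that. Some 64% to 71% of such comparisons would not be significant, unselected estimates are not inflated, and the ratio is only about 1.06 to 1.16 if the true effect is 1.2.

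**What to change.** Decide which trial this is, and make every section say so.

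**If the feasibility label is kept:**
- Name as feasibility outcomes recruitment (60 patients within the 1.5 years given in the Overview), retention to the week-4 visit, and treatment use. Build them on the counts that the Figure 1 legend already registers.
- Set the dropout mark only after reconciling the 5-10% expected under Missing Data with the roughly 20% allowed in the Sample Size Calculation.
- Report the hormone and sleep contrasts as estimates with 95% confidence intervals.
- Bring five places into line: the efficacy aim in Background and Rationale, the description of the sample as large in the Overview, the 80% power statement, the two-analysis rule under Missing Data, and the superiority wording in the Conclusion.

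**If the label is deleted:** restate the power for the chosen d = 0.6. On the t-test basis used here it is 29% to 36% at the planned size, and 80% would need about 45 per arm.

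The trial has not started and is not yet registered, so the first route costs only changes of wording and the reporting of counts already kept. Its downside is a more modest claim. The second route costs either an openly low power figure or a much larger trial.

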**International Registered Report Identifier (IRRID):**

PRR1-10.2196/49196

## Introduction

### Background and Rationale

Retinitis pigmentosa (RP) is the most frequent form of inherited retinal dystrophy (IRD) and the main cause of hereditary blindness, with more than 1.5 million patients affected worldwide and a prevalence of 1:4000 people [1]. The term was coined by Donders in 1857 [2] and compounds a group of heterogeneous diseases characterized by a progressive degeneration of photoreceptors, starting with rods and eventually affecting cones as well. This is the mechanism responsible for the progressive loss of vision function [3].

RP can have bilateral or, less frequently, unilateral involvement and can occur isolated or as part of a syndrome [1,4,5]. It is caused by more than 3000 mutations in over 70 genes, creating a wide heterogeneity among patients with RP [6].

RP affects mainly the outer retina, but in the final stages of the disease, atrophy and damage ultimately affect the inner retina, including retinal ganglion cells [7]. Intrinsically photosensitive retinal ganglion cells (ipGCs) constitute a special type of photoreceptors within the retina that contain the melanopsin photopigment [8,9]. Although they represent less than 10% of the total ganglion cells, they play a key role in regulating the pupillary reflex, circadian photoentrainment, mood, and diverse cognitive functions [9-16]. Alterations in circadian rhythms, partially dependent on ipGC integrity, have been previously reported in different ocular diseases and blindness [17-22]. These patients usually do not properly receive light signals that ordinarily synchronize their internal circadian clock to the 24-hour day, causing sleep-wake cycle abnormalities and recurring blocks of days with severe insomnia and excessive daytime sleepiness [21]. This circadian clock impairment could ultimately affect the quality of life due to sleep disorders and could also involve cardiovascular problems or emotional disorders or trigger or accelerate the pathology progression in neurodegenerative diseases [7,23,24].

The few therapeutic options for patients with RP currently available in daily clinical practice just retard disease progression and are limited. There is no therapy nowadays that restores vision, so the prognosis is poor [3]. Because of the chronic nature of this disease and its disabling progression, there has been great interest in the development of new strategies to help patients cope with the social and psychological impacts of blindness.

Among nonpharmacological strategies aimed at slowing down the degenerating process are those that are based on light protection. Some pieces of evidence indicate that some hereditary pigmentary retinopathies are partly light dependent [25,26]. Violet (400-440 nm) and blue (440-500 nm) light constitute the lower wavelength of the visible spectrum, which carries the highest amount of energy per photon [27]. The possible role of short-wavelength light (SWL) in the photochemical damage to retinal tissue and retinal pigment epithelium (RPE) cells has been studied, with high-energy SWL (415-455 nm) being the most harmful to the eye (the second type of phototoxicity or blue-light hazard) [28-30]. Blue-violet light could cause oxygen-dependent retinal injury, acting on specific chromophores, and *N*-retinylidene-*N*-retinylethanolamine (A2E) is considered the most important target molecule. Reactive oxygen species (ROS) initiate the activity of cysteine-dependent proteases, ultimately leading to apoptosis and cell death [28,31-34]. Mitochondria from photoreceptors, retinal ganglion cells, and RPE cells are the main targets of blue light–associated oxygen free radicals [35-37]. Moreover, photophobia, a common unpleasant symptom in patients with RP, has been described to be caused primarily by SWL in its interaction with S-cones from the retina [38]. In addition, in experimental RP models, limiting SWL exposure by the application of optical filters has been demonstrated to slow retinal degeneration [39].

However, some studies have shown that longer blue wavelengths of the visible spectrum (465-495 nm) are essential for the circadian rhythm, pupillary reaction, color discrimination, and night vision [7,23,24,40-43]. Numerous studies have demonstrated their close association to circadian rhythm regulation, alertness, memory, and cognition [44,45]. Therefore, blue-light exposure could regulate the secretion of melatonin in the pineal gland through the retinal–suprachiasmatic nucleus (SCN)–pineal axis, modulating cortisol expression through the hypothalamic–pituitary–adrenal (HPA) axis or the autonomous nervous system [7,23,24,44]. These responses are driven primarily by intrinsically photosensitive retinal ganglion cells (ipGCs), which are more sensitive to 480 nm SWL and remain functional in late stages of the disease [7]. In contrast, melatonin suppression has a peak sensitivity of roughly 460 nm in humans, the same spectrum that has been shown to reset the circadian pacemaker and directly enhance alertness [46].

In consequence, evening SWL exposure in daily life may affect sleep, hormone release, and the circadian rhythm in patients with RP. In fact, it has been reported that wearing SWL-blocking glasses that virtually eliminate SWL is effective in improving sleep, the circadian rhythm, and mood. Three randomized controlled trials (RCTs) have demonstrated that SWL-blocking glasses bring about significant improvement in sleep quality in participants with insomnia [42,43,47].

Among pharmacological interventions, the trophic and antioxidant effects of vitamins or nutritional supplements have been evaluated in patients with RP to demonstrate a protective action on cone death [48-50]. Accumulating evidence indicates that melatonin therapy is a promising approach in the treatment of various ocular degenerative disorders (eg, age-related macular degeneration, diabetic retinopathy, and RP) since it can exert a protective effect against damage to RPE cells evoked by ROS, but it has also been reported to increase ROS-induced damage to photoreceptors and RPE cells [51-55].

Melatonin is an endogenous hormone that has been implicated in a variety of biological processes, including antioxidant, anti-inflammatory, and neuroprotective activities [56,57]. Melatonin is released from the pineal gland in a circadian fashion, which is controlled by the SCN. However, many other tissues and organs also synthesize melatonin. In the retina, it is mainly synthesized by photoreceptors and is involved in the modulation of neuronal activities. Its circadian production results in a high concentration at night and a low level during the day, although its amount is small compared to its pineal counterpart [7,51,58].

Oxidative damage has been proposed to be an important contributor to cone death in RP, and antioxidants may prevent cone damage in RP by reacting with free radicals produced during light absorption [59]. Melatonin behaves like synthetic mitochondria-targeted antioxidants, which are concentrated in the mitochondria at relatively high levels [51,58]. It exerts its antioxidant actions in the eye via several mechanisms, including direct ROS scavenging, stimulating antioxidant enzymes, improving the functioning of the mitochondrial electron transport chain (ETC), reducing the extent of electron leakage from the mitochondrial complexes, and improving the efficacy of other antioxidants. As mentioned before, mitochondria from photoreceptors, retinal ganglion cells, and RPE cells are the main targets of ROS produced by the ETC, and thus, melatonin may prevent mitochondrial damage in patients with RP [7,51,58,60,61].

However, it has also been demonstrated that daily administration of appropriately timed melatonin can synchronize the circadian clock [62-66] in patients with sleep disorders; its use is even recommended by the Standards of Practice Committee of the American Academy of Sleep Medicine [67]. The phase-shifting effects of melatonin are essentially opposite to those of light. It can phase-shift the endogenous circadian clock and, in the absence of light, entrain the sleep-wake and neuroendocrine rhythms (cortisol) [61]. Therefore, it is likely that OM may also be effective in sleep and circadian rhythm management in patients with RP. However, to the best of our knowledge, no previous RCT has investigated the potential additive benefits of adjunctive SWL-blocking glasses plus OM in improving sleep, perceived stress, and the circadian rhythm in patients with RP.

The aim of this study is to assess the efficacy of OM combined with SWL-blocking filters in patients with RP who have sleep disorders and stress compared to any intervention alone or no intervention. We hypothesized that both interventions would improve their sleep quality, reduce their perceived stress levels, and shift their circadian rhythm to morningness.

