##### Questionnaires and Diaries

The State-Trait Anxiety Inventory (STAI), the Epworth Sleepiness Scale (ESS), the Pittsburgh Sleep Quality Index (PSQI) questionnaires and a sleep diary will be used to ask patients about their level of sleep quality, perceived stress, and anxiety.

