##### Sleep Diary

During the 2-week period before trial commencement and the 4-week period of the intervention, patients will fill a daily self-recorded sleep diary at home. The sleep diary will record parameters such as bedtime, wake time, sleep onset, and sleep offset time.

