##### State-Trait Anxiety Inventory

STAI is designed to assess the degree of state and trait anxiety in research participants (in this study, patients with moderate and severe RP) and takes about 10 minutes to complete. It is a reliable, valid, and responsive questionnaire consisting of 20 items for assessing state anxiety and 20 for trait anxiety. Higher scores (maximum score of 40) are positively correlated with higher levels of anxiety [85]. To evaluate the magnitude of any treatment effect, the minimum clinically important difference (MCID) will be regarded as a 30% reduction from baseline [86]. This magnitude represents a “small” effect in the behavioral sciences.

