#### Statistics

A linear mixed effect regression model will be applied to compare intervention arms against the control at baseline and stimulated measures for the HPA axis or the retinal–SCN–pineal axis comprising cortisol, melatonin, and sAA [106]. Baseline characteristics of patients from each group will be compared applying independent *t* tests, 2-way repeated-measures ANOVA, and the Fisher exact test. To grade the RP severity (by quantifying clinical features, the ETDRS score, and visual field deviation) and the primary outcomes, we will consider both to be continuous variables and apply a multiple linear regression model. For secondary outcomes, normally distributed variables will be statistically assessed via parametric tests, such as the *t* test or ANOVA, while nonnormal distributed variables will be assessed with nonparametric tests, such as the chi-square test or the Fisher exact test and the Mann–Whitney U test. A chi-square or Fisher test will be performed to compare STAI, PSQI, and ESS scores among groups.

Statistical associations between covariates and outcomes will be evaluated using the appropriate statistical methodology, as previously described. Multivariable linear regression models will be appropriately fitted to continuous data based on the distributions of those data. Multiple logistic regression models will be fitted for all dichotomous outcome variables. Appropriate variable selection methods and model fit statistics will be used to determine the best-fitting model to determine the effects of treatment after adjusting for significant effects of covariates.

Finally, any protocol amendment will be first submitted to the Institutional Review Board for approval. If the amendment changes anything about what is reported

on ClinicalTrials, then the study’s registration on ClinicalTrials will be updated accordingly.

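### The hypothesised shift to morningness has no timing endpoint, and because controls keep no diary during the intervention it cannot be compared with control

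*Protocol article*

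**What the plan says.** **Hypothesis.** Background and Rationale ends with: "We hypothesized that both interventions would improve their sleep quality, reduce their perceived stress levels, and shift their circadian rhythm to morningness". The aim stated just before it sets the combination against each intervention alone and against no intervention.

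**Outcomes.** Primary Outcome Measures lists changes from baseline in "hormone release (sAA, cortisol, and melatonin levels in salivary and hair samples) and sleep quality, as measured by the ESS and the PSQI". Secondary Outcome Measures names visual and retinal tests and adds that "several patient-reported variables, such as self-recorded sleep diaries, perceived stress, and functional status will be recorded".

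**Diary.** Under Sleep Diary: "The sleep diary will record parameters such as bedtime, wake time, sleep onset, and sleep offset time". That section asks patients for a diary in the two weeks before the trial and the four weeks of intervention, without distinguishing arms. The Methods Overview requires the intervention-period diary only of the three active arms. Table 1 enters none for controls in that period, and the No Intervention section limits controls to a single two-week block.

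**Samples.** Laboratory Assessment sets collection between 9:00 A.M. and noon. The saliva section plans two samples per patient in 24 hours.

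**The concern.** A shift to morningness is a statement about when the body clock runs, not about how well a patient sleeps or how much hormone is present. Testing it needs a variable measured in clock time, at baseline and during treatment, in every arm that is to be compared. The outcome sections name no such variable.

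Two things are at stake. First, part of the stated hypothesis has nothing against which it can succeed or fail. Hormone levels or single diary times could later be offered as support without having been designated for that purpose. Second, the comparison with no intervention, which is part of the aim, would lack control data on timing. Once the trial has run, no analysis plan can supply diaries that were never kept.

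**Working it through.** The plan gives no figure on this point, so the check sets each hypothesised effect beside the outcome and data meant to test it.

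| Hypothesised effect | Listed outcome | Instrument | Data in all four arms, before and during treatment? |
|---|---|---|---|
| Sleep quality | Primary | ESS, PSQI | Yes: V0 and V4 (Table 3) |
| Perceived stress | Secondary | None assigned in the outcome list; STAI is nearest | STAI: V0 and V4 (Table 3) |
| Shift to morningness | None | None | Diary times in the active arms only |

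**Can the hormones serve as a timing measure?** They are defined as levels. With the period fixed at 24 hours, a simple rhythm curve has three unknowns (mean, amplitude, time of peak). Two samples per visit cannot determine three unknowns, least of all inside a three-hour morning window (9:00 to 12:00). A changed morning level could reflect a different amplitude or mean as easily as a different phase. Pooling the weekly visits would require phase to stay constant, which is what the hypothesis denies.

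**Can wearables serve?** The abstract lists wearable sleep data, but the Limitations section says that trackers are not part of the protocol. They cannot be relied on.

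**Can the diary serve?** It can in the active arms. For each night, mid-sleep M = (sleep onset + sleep offset) / 2, on a clock that runs continuously through midnight. For each patient, the change is D = mean M over the last two intervention weeks − mean M over the two baseline weeks. A negative D is a move towards morningness. The contrast wanted is mean D (active) − mean D (control).

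For controls the second term does not exist. Table 1 places their only diary block before the intervention. The No Intervention section can be read as placing it after the trial starts. On either reading there is one block, and a change needs two.

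**What can be compared.** Four arms give 4 × 3 / 2 = 6 pairs. Three involve control and cannot be estimated on D; the other three are between active arms. With the planned 15 patients per group, 45 of 60 would have diaries in both periods. The combination against OM shows what the filters add on top of melatonin, and the combination against SWL shows what melatonin adds on top of the filters. Neither gives the effect of an intervention alone unless the two effects simply add up. Whether they do is a question the Choice of Comparators section sets out to answer.

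**Perceived stress.** Questionnaires and Diaries treats the STAI, ESS, PSQI and diary as one set: "a sleep diary will be used to ask patients about their level of sleep quality, perceived stress, and anxiety". The ESS and PSQI are described as sleep questionnaires, which leaves the STAI. The plan says "STAI is designed to assess the degree of state and trait anxiety in research participants". It gives the STAI a threshold ("the minimum clinically important difference (MCID) will be regarded as a 30% reduction from baseline") and a planned test ("A chi-square or Fisher test will be performed to compare STAI, PSQI, and ESS scores among groups"), yet neither outcome list names it.

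**The case against.** The best reply is that this is a condensed article. Morningness occurs once, in a background sentence; the abstract's objective speaks of stress and sleep problems, and neither conclusion promises a phase shift. Sleep diaries are a listed secondary outcome and record four clock times, so timing data are declared, and the formula for a summary variable is commonly left to the full protocol or analysis plan.

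Much of this stands. A missing formula alone would not be a finding. What remains is the control arm: the design as stated collects no intervention-period diary there, and no later document can derive an endpoint from it.

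Several stronger readings are tempting and not supported:

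- A reader might infer that the stress hypothesis has no endpoint. Perceived stress is a named secondary outcome, and the questionnaire set is linked to it; only the assignment of an instrument is missing.
- A reader might infer that the hormones are unrelated to the hypothesis. The Significance section speaks of biochemical stress, and the Discussion ties cortisol and sAA to stress and all three markers to circadian patterns. They are relevant as mechanism, but their levels do not measure phase.
- A reader might infer that morningness cannot be examined at all. The active arms can be compared with one another.
- A reader might put a false-positive rate on choosing among the four diary times afterwards. Nothing shows that the investigators would do so, and bedtime with sleep onset, and wake time with sleep offset, are too closely paired to be treated as independent.

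**Conclusion.** The point holds for circadian timing. One of the three hypothesised effects has no defined endpoint, and none of its three comparisons with control can be estimated as designed. For perceived stress the gap is one of wording.

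This rests on two assumptions: that the morning collection window, stated once under Laboratory Assessment, applies at every visit; and that the Overview, Table 1 and the No Intervention section govern the control diary, not the general sentence under Sleep Diary. If controls were in fact to keep the diary throughout, only the derived variable would be missing, and the point would be minor.

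The trial had not started when the article was written, so the change can still be made before any data are lost.

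**What to change.** 1. In Secondary Outcome Measures, pre-specify one timing endpoint: change in mean mid-sleep time (midpoint of diary sleep onset and offset) from the two baseline weeks to the last two intervention weeks.
2. Have controls keep the same diary in the two baseline weeks and throughout the four weeks of intervention, and bring Table 1, the Overview, the Sleep Diary section and the No Intervention section into line.
3. If the control diary is not wanted, delete the morningness limb of the hypothesis. In either case, describe hormone levels as mechanism and not as evidence of a phase shift.
4. As a wording alignment, name the STAI state score change from V0 to V4 in Secondary Outcome Measures and label it as anxiety.

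**Cost.** Items 1, 3 and 4 need protocol wording and one derived variable. Item 2 adds 4 × 7 = 28 diary days per control patient, or 15 × 28 = 420 across the planned control group. That is a small extra burden, on patients who otherwise have little to do for the trial between visits. It makes the comparison with control estimable; it does not settle how comparable the control group is, which depends on how that group is formed.
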